Hypersensitivity	Mild reaction not requiring treatment	**I**
	Mild/moderate/severe reaction treated with medication (e.g. antihistamine and/or steroid and/or adrenaline)	**II**
	Anaphylactic shock	**IV** (**a** or **b** depending on organ dysfunction)
Air embolism	By definition clinically evident air embolism results in cardiorespiratory dysfunction	**IVb**
Pneumothorax/haemothorax	Small pneumothorax managed without a chest drain	**I**
	Pneumothorax/Haemothorax without respiratory failure requiring chest drain	**IIIa**
	Evidence of respiratory failure or any other organ dysfunction	**IV** (**a** or **b** depending on organ dysfunction)
Pulmonary embolism	Small PE without evidence of respiratory failure managed with anticoagulation only	**II**
	Evidence of respiratory failure or any other organ dysfunction	**IV** (**a** or **b** depending on organ dysfunction)
Deep vein thrombosis	Managed with anticoagulation only	**II**
	Need for endovascular intervention including filters not under GA	**IIIa**
	Need for endovascular intervention or surgical thrombectomy under GA	**IIIb**
Lower respiratory tract infection (including aspiration)	Managed with physiotherapy only	**I**
	Managed with antibiotics	**II**
	Evidence of respiratory failure or any other organ dysfunction	**IV** (**a** or **b** depending on organ dysfunction)

*GA* general anaesthesia

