### Blinding

Patients, clinical outcome assessors, ward staff and research staff both centrally and at the site will be blinded to the allocation. Only members of the surgical team present in the theatre when the allocation is revealed will know which treatment arm the patient has been allocated to. These individuals are not permitted to inform colleagues or assess trial outcomes. The operation note, medical case notes and any other documentation that leaves the operating theatre will not state the allocation. The effectiveness of this blinding strategy will be assessed using blinding indices.

The patient will be unblinded if they suffer a serious adverse event and knowledge of the allocation is required for the ongoing medical management of the condition. It is unlikely that this trial will require unblinding as the FS is administered only once in the theatre environment. A severe hypersensitivity reaction, air embolism or transmission of an infective agent constitute a serious adverse event. If they occur, severe hypersensitivity and air embolism would be anticipated to occur during or immediately after administration in the theatre setting. Staff caring for the patient at this time will not be blinded, so there will not be a delay in diagnosis and emergency management.

In the event that the patient is diagnosed with an infectious disease that was not diagnosed pre-operatively, they will be unblinded. Based on the ‘Serious Hazards of Transfusion’ 2017 annual report [24], the following infectious diseases are known to have been transmitted via blood products in the UK:
Hepatitis A, B, C or EHuman immunodeficiency virus (HIV)Parvovirus (B19)Cytomegalovirus (CMV)Human T cell lymphotropic virus (HTLV) types I and IIMalariaVariant Creutzfeldt-Jakob Disease (vCJD) or any other prion disease

If the patient is newly diagnosed with any of the above infectious diseases, they will be unblinded and immediately referred to the appropriate medical specialists for treatment.

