### Safety

Surgical complications and adverse reactions to fibrin sealant that are Clavien-Dindo grade IV or above (see Tables 2 and 3) will be the only events reported to assess safety. As the ‘Clavien-Dindo Classification of Surgical Complications’ constitutes a primary outcome measure for the DEFeND pilot trial, the presence of post-operative complications along with their grade will be recorded on the eCRF. All complications related to the neck dissection surgery and/or use of fibrin sealant that are Clavien-Dindo grade III-b or below that meet the definition of serious are exempt from Serious Adverse Event (SAE) reporting. Such events are ‘expected’ and should only be recorded in the relevant section of the eCRF.

Post-operative complications related to either neck dissection or use of fibrin sealant that are Clavien-Dindo grade IV or above are ‘unexpected’ for the DEFeND trial. The LCTU will notify the main REC of all Suspected Unexpected Serious Adverse Reactions (SUSARs) occurring during the study according to the following timelines; fatal and life-threatening within 7 days of notification and non-life-threatening within 15 days. All investigators will be informed of all SUSARs occurring throughout the study.

Site staff (with the exception of the surgical team) will be blinded; therefore, the SAE reporting form will not state which arm the patient has been randomised to. For the purposes of SAE reporting, it should be assumed that the patient was randomised to receive fibrin sealant (i.e. interventional arm). Causality should be assigned to the following:
AnaestheticGenerality of surgery (including surgical airway, primary tumour resection)Neck dissection surgeryUse of fibrin sealant

Pregnancy is listed as an exclusion criterion for entry to the DEFeND trial. In the event of a patient becoming pregnant after recruitment to the trial, this fact should be reported in the same way as an SAE. The guiding principles in this event are as follows:
If the patient has not yet received treatment, or completed treatment, the patient may be withdrawn from the trial.Once treatment is complete, i.e. the patient is in follow-up phase, it may well be possible to retain the patient to the conclusion of the trial.A decision will be made in the best interests of the patient between the treating clinician and the Chief Investigator as to retention in the trial and any continuing cancer therapy.

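### A severe sealant reaction short of shock is named an SAE under Blinding, but its Table 3 grade of II takes it out of SAE reporting under Safety

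*Protocol article*

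**What the plan says.** The Blinding section of the protocol article states: "A severe hypersensitivity reaction, air embolism or transmission of an infective agent constitute a serious adverse event". It attaches no Clavien-Dindo grade to this statement, which stands in the account of when a patient is to be unblinded.

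Table 3, in the section on the Clavien-Dindo classification, has three hypersensitivity rows. A mild untreated reaction is grade I. The next row, "Mild/moderate/severe reaction treated with medication (e.g. antihistamine and/or steroid and/or adrenaline"), is grade II. "Anaphylactic shock" is grade IV. Air embolism is fixed at IVb, because "By definition clinically evident air embolism results in cardiorespiratory dysfunction". There is no row for transmitted infection.

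The Safety section says that surgical complications and sealant reactions of grade IV or above "will be the only events reported to assess safety". Its exemption covers "All complications related to the neck dissection surgery and/or use of fibrin sealant" and applies to those "that are Clavien-Dindo grade III-b or below that meet the definition of serious are exempt from Serious Adverse Event (SAE) reporting". Exempt events are labelled expected and "should only be recorded in the relevant section of the eCRF". Related complications of grade IV or above are labelled unexpected. Suspected unexpected serious adverse reactions (SUSARs) go to the ethics committee within 7 days if fatal or life-threatening and within 15 days if not.

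**The concern.** The exemption is set by surgical severity grade. That suits a haematoma or wound infection, which any neck dissection can produce. It suits a reaction to the study product less well, because Table 3 grades by the treatment given, and a reaction that the protocol itself calls severe and serious can be treated with drugs alone and so be graded II. The harms that the Blinding section singles out are those most specific to the sealant, yet the grade rule can leave them without an SAE report.

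This matters because the trial has no independent data monitoring committee. Under Data monitoring, the independent TSC members review the interim safety data and advise on whether to continue, and safety is the only ground on which they are expected to recommend stopping. The section on progression to phase III lists safety of the intervention among the variables that inform that decision.

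**Working it through.** No formula applies, and the plan gives no figure to reproduce. The check is to follow each harm named under Blinding through Table 3 and then through the Safety rule, taking it as related to the sealant.

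| Event | Blinding | Table 3 | Result under Safety |
|---|---|---|---|
| Severe hypersensitivity, treated with medication, no shock | SAE | II | Expected; no SAE report; eCRF only; outside the events reported to assess safety |
| Severe hypersensitivity reaching anaphylactic shock | SAE | IV (a or b) | Unexpected; reported |
| Clinically evident air embolism | SAE | IVb | Unexpected; reported |
| Transmitted infection | SAE | No row | Not determined |

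**Hypersensitivity.** The three places agree for shock and part company for a severe reaction short of it. The first row needs no inference: Table 3 names both severe reactions and adrenaline in its grade II entry, and the exemption expressly includes complications of sealant use.

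**Transmitted infection.** Nothing in the article grades it. If a site fell back on the generic wording of Table 2, an infection needing drug treatment would be II, and only a life-threatening one would be IV. On that assumption, an infection attributed to the sealant and below IV would be exempt. Blinding nevertheless treats a new diagnosis of any listed infection as reason to unblind and refer at once. The firm conclusion is only that its reporting status is open and may fall under the exemption.

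**SUSAR timelines.** (1) A SUSAR must be unexpected. (2) Under the grade rule, a sealant-related complication is unexpected only at IV or above. (3) Table 2 defines IV as life-threatening and V as death. (4) The 15-day timeline is for SUSARs that are not life-threatening. For sealant-related complications that category is therefore nearly empty: at most it holds an event that Table 3 places at IV but that is not judged life-threatening in the individual case.

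**Route to the reviewers.** Data monitoring gives the independent TSC members all interim safety data. Safety limits the events reported to assess safety to grade IV or above. The article does not say whether a grade II sealant reaction held on the eCRF is part of what they see.

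**The case against.** The strongest reply is that the texts can all be obeyed together. The exemption expressly foresees events that are serious and still not reported as SAEs, and Blinding uses the SAE label to decide on unblinding, not to create a reporting duty. A reader might infer a strict contradiction; the documents do not support that. What remains is a conflict of purpose: the harms picked out as serious for one purpose can drop out of sight for another.

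Four further limits stand.

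- A reader might take the exemption to cover every event at IIIb or below. It covers only complications related to the neck dissection or the sealant; the anaesthetic and the surgery in general are separate causality categories in the same section.
- A reader might infer that these events are lost. They are not: complications are assessed at every postoperative encounter and recorded with their grade on the eCRF. What is lost is the SAE report and a clear path to safety review. Emergency care is also unaffected, since Blinding expects such reactions to occur in front of unblinded theatre staff.
- A reader might state as fact that transmitted infection is grade II. That is an inference from Table 2, and Table 3 claims to list only common complications.
- A reader might ask that expectedness be judged against product reference information. That information is not in the documents. Since Data monitoring describes the risks as known, such a test could reduce SUSAR reports rather than increase them.

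It can also be said that the article condenses a fuller protocol and that the pilot makes no formal safety comparison between arms. The first point would excuse missing detail, but here the grades, the exemption and the list of SAEs are all stated. The second does not remove the need for safety oversight while the trial runs.

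**Conclusion.** The concern holds in a limited form. Of the three sealant harms named as SAEs, one (air embolism) has a consistent reporting status, one (severe hypersensitivity) is reported only if it reaches shock, and one (transmitted infection) has no determinable status. The expectedness rule also leaves the 15-day SUSAR timeline with almost nothing to apply to among sealant-related complications.

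The hypersensitivity conclusion rests on the stated text alone, for a reaction attributed to the sealant. The infection conclusion rests on the absence of a Table 3 row, and the possible exemption on an assumed use of Table 2. No event rate is given, and the risks are described as very rare, so the number of patients affected may well be none. The weight of the point lies in the oversight of a trial without an independent data monitoring committee, not in an expected count.

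**What to change.** Reconcile Table 3, Blinding and Safety in one short amendment:

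- Give severe hypersensitivity, air embolism and transmitted infection a single reporting status, and take all three out of the IIIb-or-below exemption. The exemption can stay for the anticipated complications of neck dissection.
- State the status of transmitted infection explicitly, since Table 3 does not cover it.
- Bring the expectedness rule and the 15-day SUSAR timeline into line with each other.
- Say that these three harms, whatever their grade, are part of the interim safety data that the independent TSC members review.

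The Clavien-Dindo grades themselves and the clinical handling of these events need not change for this purpose. The cost is a small safety-section amendment with a matching prompt on the eCRF or SAE form, and very few extra reports.

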### Dissemination policy

The results of the pilot trial will be reported in peer-reviewed journals, in a report to the funder and as a lay summary to participants. We will apply authorship criteria established by the International Committee of Medical Journal Editors.

## Discussion

The key challenges that are anticipated in the DEFeND external pilot trial are common to many surgical RCTs and can be encapsulated within three broad headings: barriers to recruitment, complexity of the intervention and adherence to the protocol.

### Barriers to recruitment

Kaur et al. described the barriers to recruitment for surgical trials in Head and Neck Oncology by conducting a survey of investigators from three of the earliest trials within the National Institute of Health Research (NIHR) portfolio [15]. Given that UK-based surgical trials in Head and Neck were in their relative infancy, all of these trials faced challenges with recruitment. The most commonly perceived barriers were lack of equipoise amongst patients demonstrated by a refusal to participate due to an expressed treatment preference, patient consent refusal owing to aversion to randomisation, excess complexity and amount of information provided to patients and lack of time in the clinic. All of these barriers are related to how investigators communicate the premise of the trial to patients. The ‘Merseyside Head and Neck Cancer Patient Research Forum’ is comprised of patients who have undergone treatment for head and neck cancer and was setup specifically to facilitate patient and public involvement in research. The PIS and informed consent forms (see Additional files 2 and 3) have been successfully passed through the forum to ensure they are easily understood while delivering sufficient detail and conveying equipoise.

Given the increase in complexity of the UK clinical trials, trials with overlapping inclusion criteria might also present a barrier to recruitment. Aintree University Hospital has a very research active Head and Neck Surgery Department, and it is possible that patients will be offered more than one study to participate in. This may result in patients suffering from excessive research burden resulting in consent refusal across the board. A predetermined hierarchy of recruitment has been decided amongst all the CI/PIs of the competing studies to enable investigators to minimise the risk of research burden.

The pilot and feasibility outcomes in the DEFeND external pilot trial will allow an in-depth analysis of recruitment and identify any further barriers. This will inform the design and execution of the phase III trial and attempts to mitigate these barriers will be made.

### Complexity of the intervention

One of the differences between surgical trials and pharmacological trials is the complexity of the intervention. Surgical interventions are multi-faceted and depend on the performance of the wider healthcare team in addition to the skill, experience and decision making of the operating surgeon. Outcomes in the DEFeND study are dependent on the perioperative management of patients; the neck dissection surgery itself; the need for other synchronous surgical procedures e.g. resection of the primary tumour; and the intervention itself. As the administration of FS is considered SOC, it is expected that randomisation will balance the variables equally across both arms.

In order that surgeons administer FS in a standardised way, a video has been produced and laminated sheets hung up in operating theatres providing temporal detail of the protocol. Many surgeons will be experienced at administering FS, but for those that are not ‘ad hoc’, training will be available. It is recognised that surgeon level performance will vary and as such the ideal standard procedure will not be replicated on each occasion. Currently, there are no requirements for surgeons to perform the surgery/administer FS a minimum number of times or achieve a predetermined standard. This is primarily to reflect the ‘real-world’ nature of the study. If the impact of the learning curve is clearly demonstrated in the pilot data, then surgeons acquiring a certain level of expertise to participate in the phase III trial will be considered.

### Adherence to the protocol

While every effort has been made to harmonise the protocol with standard clinical/research practice, there will inevitably be some challenges with adherence.
i)The use of eCRF is new to both research sites and requires real-time data entry. This will require training and logistical planning by sites to ensure there are sufficient research staff available (including weekend cover).ii)The allocation needs to be revealed at a specific time point during surgery. This requires surgeons to access their email, login to the randomisation software (TARDIS) and reveal the allocation. To minimise performance bias, the allocation must not be revealed too early; this will be monitored by recording the date and time the allocation is revealed and cross-referencing this with the start and finish times of surgery.iii)The blinding strategy may be difficult to enforce within busy clinical practice. The surgeons present in theatre at the time of the allocation reveal are not allowed to assess trial outcomes. In standard clinical practice, it is routine for the operating surgeon to review their patient post-operatively; eliminating their influence on outcomes including the patient’s perception of outcomes will be difficult. If it is known that a particular surgeon will be reviewing the patient post-operatively, they will be asked to vacate theatre at the time of the reveal.iv)Patients are required to attend two planned follow-up appointments after surgery. The first at 7–14 days to coincide with the removal of skin clips and the second at 4–6 weeks to coincide with the first routine clinic appointment. It is possible that this schedule will clash with some follow-up arrangements and necessitate patients making extra visits. A modest financial refund for travelling expenses will be offered to patients for any extra visits.

## Progression to phase III trial

This initial study aims to inform the design, feasibility and conduct of a future phase III surgical trial. The decision to progress to this future trial will be based on variables such as recruitment rate, safety of intervention, sample size estimation and ongoing surgical equipoise. It is anticipated that further amendments to the protocol will be required to fine tune the trial design based on the outcomes of this external pilot trial and feedback from sites (both research staff and surgeons). All these issues will be discussed by the TSC once the external pilot trial has closed and a decision to progress to a phase III trial made.

## Trial status

Recruitment started on November 06, 2018, and is on target to achieve at the pre-specified sample size in the scheduled 12 months. The interventions appear to be acceptable to potential participants, and approximately 50% of those who have been approached to take part have given written consent. The protocol being used is version 2.0 dated June 27, 2018.

## Data Availability

Not applicable.

## Abbreviations

AE: Adverse event
APTT: Activated partial thromboplastin time
CDC: Centre for Disease Control and Prevention
CONSORT: Consolidated Standards of Reporting Trials
eCRF: Electronic case report form
FDA: United States Food and Drug Administration
FS: Fibrin sealant(s)
GCP: Good Clinical Practice
HDU: High-dependency unit
HE: Health economics
HES: Hospital Episode Statistics
HRQoL: Health-related quality of life
ICER: Incremental cost-effectiveness ratio
ICU: Intensive care unit
IDMSC: Independent Data Monitoring and Safety Committee
INR: International normalized ratio
ISRCTN: International Standard Registered Clinical/Social Study Number
LCTU: Liverpool Cancer Trials Unit
MACRO: Electronic data capture software
MCID: Minimal clinically important difference
NDII: Neck Dissection Impairment Index
NHS: National Health Service
NIHR: National Institute of Health Research
PIS: Patient Information Sheets
REC: Research Ethics Committee
SAE: Serious adverse event
SOC: Standard of care
SPIRIT: Standard Protocol Items: Recommendations for Interventional Trials
SUSAR: Suspected Unexpected Serious Adverse Reaction
TARDIS: Treatment Allocation Randomisation Software
TSC: Trial Steering Committee
UKCRN: United Kingdom Clinical Research Network
VAS: Visual analogue scale
WHQ: Wound Healing Questionnaire
